### Sample size calculation

Sample size was calculated to estimate the occurrence of outcomes in each of the groups separately and to evaluate the association between each outcome: muscle thickness [5], IL-6 [6], TNF-alfa [7] and, quality of life [8], and the exposure variable. According to the largest sample size calculation, 36 patients would be required (to maintain a minimum power of 80% and a 95% confidence level). To compensate for possible losses and refusals, 42 patients will be included [[5], [6], [7], [8]].

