### Randomization

The randomization process will be performed using the generation of random numbers in the Stata software, version 13, and the researcher who will carry out the process will be blinded regarding to the study objectives. The randomization will be done in blocks, each block referring to the HD shift. In each block, the first patient drawn will go to the BFRG, the second to the EG, the third to the CG, and so on. In total, 14 patients will be drawn in each block to ensure balance between groups.

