### Data processing and analysis

The data will be doubled typed in EPIDATA 3.1 software, which will perform analysis to verify inconsistencies and correction of possible errors. The 5% significance level will be used and the statistical analysis will be conducted in Stata 14.0 software. The two mixed factors analysis of variance (ANOVA) will be used in the comparison of the training protocols, using Bonferroni as a post-hoc test for parametric variables. Kruskal-Wallis test and Dunn's post-hoc test will be used to non-parametric variables. The responsible researcher for the statistical analysis will be blinded regarding to the study objectives.

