## Discussion

Individuals with CKD present altered inflammation and oxidative stress parameters, show a higher concentration of inflammatory markers and oxidizing enzymes, as well as a lower concentration of anti-inflammatory markers and antioxidant enzymes than healthy subjects [21], especially when exposed to therapy of renal replacement [22]. Studies aimed to verify the effects of exercise on patients submitted to HD are not new in the scientific literature. However, data from studies with physical exercise intervention on the immune system and oxidative stress in this population are rare and inconclusive. In addition, there is no consensus of exercise recommendations for patients submitted to HD [1].

The investigation of intradialytic exercise effects per se on clinical, physiological, functional and psychological parameters plays a significant role on the relevance of the present study. Furthermore, to our knowledge, this is the first RCT to investigate the impact of intradialytic exercise with BFR on the immune system and oxidative stress of individuals with CKD during HD. In addition, this RCT also aims to verify the effects of continuous moderate exercise either using or not BFR on the quality of life, functional capacity, muscle strength and muscle thickness in patients during HD, which are affected by CKD.

The main strengths of this study will be its randomized design and the inclusion of two different exercise protocols (cycling either using or not BFR) administered in a personalized way in patients in "real situation" who suffer from various adverse effects of CKD. As this RCT encounters the expected effects of continuous moderate exercise with BFR on the different studied variables, it would, at least, generate strong evidence for the implementation of an exercise program with BFR during HD to improve general health of this population.

Thus, it is expected that the present study will generate important information about the role of intradialytic continuous moderate exercise on the clinical, physical and psychological health of patients with CKD during HD. In addition, we aim to verify if performing exercise with BFR could optimize exercise results.

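### Bonferroni after a three-arm ANOVA is valid but needlessly conservative for the three pairwise differences in change, including BFRG versus EG

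*Protocol article*

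**What the plan says.** The section Data processing and analysis of the protocol article sets the overall level ("The 5% significance level will be used"), names a two-factor mixed ANOVA for comparing the training protocols, and follows it with multiple comparisons "using Bonferroni as a post-hoc test for parametric variables". For other variables, "Kruskal-Wallis test and Dunn's post-hoc test will be used to non-parametric variables". It does not say which comparisons form the Bonferroni family, or whether post-hoc tests are barred after a non-significant omnibus test.

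There are three arms: BFRG, EG and CG. Sample size calculation gives the numbers: "According to the largest sample size calculation, 36 patients would be required" and "To compensate for possible losses and refusals, 42 patients will be included". The Discussion states the comparative aim: "we aim to verify if performing exercise with BFR could optimize exercise results". That is the BFRG-versus-EG pair.

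Most outcomes are measured at baseline and at the end. Blood is also drawn after the third training session and at the end of week six.

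**The concern.** With three pairs, Bonferroni tests each at one third of 5%. In a three-arm comparison of a single quantity this is stricter than needed. If any two of the three pairwise null hypotheses are true, all three arms are equal. The only joint hypothesis above the single pairs is therefore the omnibus null. Once that is rejected at 5%, at most one pairwise null can still be true, and testing it at 5% keeps the family-wise error at or below 5%.

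At stake is power on the comparison that gives the trial its purpose. With 12 to 14 patients per arm there is little to spare, and a real added effect of BFR is more likely to be missed under the stated rule than under an equally valid one.

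**Working it through.** **Inputs from the article.** Level 5% (two-sided assumed). Power target: "to maintain a minimum power of 80% and a 95% confidence level". Patients per arm, assuming an equal split: 36/3 = 12 analysed and 42/3 = 14 enrolled.

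**Assumed.** The article gives no effect size or SD, so its 36 cannot be reproduced. Effects are therefore expressed in SDs of change, normally distributed with equal variance. Solving for 80% power at two-sided 5% in a two-sample t test with 12 per arm gives d of about 1.20, used here as a reference. A smaller effect of 0.6 SD is also shown.

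**Analytic check.** The non-centrality is d × √(n/2) = 1.2 × √6 = 2.94.
- Two-sample t test, 22 df: power 80.2% at 5% (critical t 2.07) and 63.8% at 1.67% (critical t 2.59).
- Error pooled over three arms, 3 × 11 = 33 df: 81.4% at 5% (critical t 2.03) and 66.2% at 1.67% (critical t 2.52).

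The 66.2% is the Bonferroni power. The 81.4% is only an upper limit for a valid rule: unadjusted tests with no omnibus condition have a family-wise error of about 12%.

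**Simulation** (200,000 trials per scenario, pooled error). With two visits, the group-by-time F test equals a one-way ANOVA on change. The closed test means omnibus F at 5%, then each pair at 5%. The last column is closed minus Bonferroni.

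| Mean change CG, EG, BFRG (SD) | Pair | n per arm | Bonferroni | Holm | Closed | Gain (points) |
|---|---|---|---|---|---|---|
| 0, 0, 0.6 | BFRG-EG | 12 | 16.2% | 17.4% | 21.7% | 5.5 |
| 0, 0, 1.2 | BFRG-EG | 12 | 66.2% | 69.6% | 76.9% | 10.7 |
| 0, 0.6, 1.2 | BFRG-EG | 12 | 16.2% | 20.8% | 28.6% | 12.4 |
| 0, 0.6, 1.2 | BFRG-CG | 12 | 66.2% | 67.0% | 70.2% | 4.0 |
| 0, 0.6, 1.8 | BFRG-EG | 12 | 66.3% | 74.4% | 81.1% | 14.8 |
| 0, 0, 0.6 | BFRG-EG | 14 | 19.5% | 20.9% | 25.8% | 6.3 |
| 0, 0, 1.2 | BFRG-EG | 14 | 74.8% | 78.0% | 84.1% | 9.3 |
| 0, 0.6, 1.2 | BFRG-EG | 14 | 19.2% | 24.8% | 33.0% | 13.8 |
| 0, 0.6, 1.2 | BFRG-CG | 14 | 74.7% | 75.3% | 77.9% | 3.2 |
| 0, 0.6, 1.8 | BFRG-EG | 14 | 74.5% | 82.1% | 87.0% | 12.5 |

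The 14.8 points do not depend on dropping the omnibus condition: with means 0, 0.6 and 1.8 the omnibus test is significant in 97.7% of trials. Where power is already very high, little can be gained (BFRG-CG in that scenario, 12 per arm: 96.6% to 97.6%). Making Bonferroni itself conditional on the omnibus test changes its power by at most about 0.3 points.

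**Family-wise error, 12 per arm.** All arms equal: Bonferroni 4.3%, Holm 4.3%, closed test about 5%. One arm differing by 1.2 SD: 1.7%, 3.4% and 5.0%.

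**Where the argument stops.** It covers three pairwise contrasts of one quantity. A further simulation used a mixed ANOVA with 14 per arm and an assumed within-patient correlation of 0.6. Unadjusted arm comparisons at each time point, made after a significant interaction with one arm changing, had a family-wise error of 11% to 15% with two times, 17% to 23% with three and 22% to 29% with four. Bonferroni over those same tests stayed at or below 3.3%. Adding unadjusted within-arm comparisons took the error to between 16% and 58%.

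**The case against.** The strongest reply is that nothing in the plan is wrong. Bonferroni is conventional, controls the error, and comes with simultaneous confidence intervals that match its tests. That stands: this is an efficiency point.

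A second reply is that the family is not stated. After a two-factor mixed ANOVA, post-hoc tests may compare arms at each time or times within an arm, where the omnibus test gives no such protection and Bonferroni does real work. Up to six of the eleven dependent variables are blood markers that could have more than two time points. This also stands, and it limits the point to differences in baseline-to-final change. A reader might infer that the omnibus test makes every post-hoc adjustment redundant. The stated model does not support that.

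Third, a reader might infer that power is being lost for nothing. That is too strong. For a truly null pair, the false-positive rate rises from about 1.7% to as much as 5% within each outcome, and there are eleven dependent variables. The matching intervals are also given up.

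Fourth, the size depends on assumed effects, and quoting only the larger gains would be selective. The table therefore includes the comparisons where the gain is 3 to 6 points.

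Finally, a reader might extend the point to Dunn's test for rank-analysed variables. The article does not say what adjustment accompanies Dunn's test, and no calculation here shows a loss, so no change to it is proposed.

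**Conclusion.** The point holds as a cheap improvement to a valid rule. For the three pairwise arm differences in baseline-to-final change, Bonferroni is stricter than a three-arm design requires. Moving to the closed test gains about 4 to 15 points of pairwise power at 12 per arm and about 3 to 14 at 14 per arm, in the comparisons tabulated. Holm gains about 1 to 8. Family-wise error within an outcome stays at or below about 5%.

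The figures rest on equal arms, normal changes with equal variance, and effects that the article does not supply. The validity of the closed test rests on exactly three arms, one contrast per outcome, and a binding rule to stop when the omnibus test is not significant. The point does not bear on the sample-size statement or on error control across outcomes.

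**What to change.** In Data processing and analysis, replace the Bonferroni clause for parametric variables with wording such as: *For each outcome, the family is the three pairwise arm differences in baseline-to-final change. Each is tested at 5%, only if the omnibus test of arm differences in that change is significant at 5%. Any comparisons at individual time points, within arms or at the intermediate blood draws are adjusted separately for multiplicity.*

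For blood outcomes, the omnibus test must be of the baseline-to-final change itself. A multi-time interaction can be significant because of an intermediate draw, and would then not protect the three pairs.

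If no binding stop rule is wanted, name Holm in place of Bonferroni. It needs no omnibus test and rejects everything that Bonferroni rejects.

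The cost is one or two sentences, with no new data or patients. Simultaneous confidence intervals will no longer match the tests, so the article should say that intervals are unadjusted or reported separately. The higher false-positive rate for a null pair, at most 5% within an outcome, should be accepted openly. Leave the Dunn clause as it is.

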## Abstract

Chronic kidney disease (CKD) is associated with physical weakness and increased oxidative stress and inflammation levels. Rehabilitation programs are associated with an improvement in the functional capacity, inflammatory and oxidative stress profile. Exercise associated with blood flow restriction (BFR) has been demonstrating positive effects in training programs, but there is lack information about exercise with BFR in CKD. Therefore, the aim of the present study is to describe a protocol using continuous moderate exercise with blood flow restriction (BFR) applied during hemodialysis (HD) to measures health indicators and immune system and oxidative stress parameters in CKD patients. Methods: A RTC will be conducted with 42 patients in HD. Baseline measures will be compared with final measures (anthropometric, cardiorespiratory, biochemical, muscle fitness, nutritional and behavioral questions). Participants will be randomly allocated to: 1) Continuous moderate exercise group with BFR; 2) Continuous moderate exercise group without BFR; 3) Control group without exercise. The intervention will be 12 weeks long during HD session. Patients will perform 20 min of continuous moderate exercise on a stationary bicycle three times a week. The present study is expected to generate significant information about the role of exercise with BFR in patients with CKD during HD.

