A trained nurse will draw 10 mL of blood directly from intravenous fistula, 5 mL in the tube with clot activator and another 5 mL in the anticoagulant tube. The blood will be separated and stored. The erythrocytes fraction will be isolated and stored to oxidative stress analyses. Blood samples will be collected at baseline and repeated after the third training session (baseline blood lactate concentration after training) and after the end of the last training session of each training mesocycle, at the end of weeks six and twelve, respectively. The last blood collection will be performed 48 h after the last exercise session, to avoid acute effects of the exercise influencing inflammatory and oxidative stress markers (Fig. 2).

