**Fig. 2 fig0010:**
[figure not shown]
Schedule of blood collections.

Serum levels of IL-6, IL-10, and CRP will be measured using immunoassay kit (DuoSet ELISA Development, R&D Systems, Inc., USA). These methods will follow the manufacturer's recommendations. The amount of IL-6, IL-10, and CRP will be determined by measuring the absorbance at 450 nm. All samples and standards will be measured in duplicate, and the coefficient of variation will be less than 5%. The IL-6, IL-10, and CRP levels will be expressed in pg/mL.

Oxidative stress markers (catalase, peroxide dismutase, and glutathione peroxidase enzymes) will be measured using a commercially available kit (RANSEL®; Randox Lab, Antrim, United Kingdom), using the method described by Misra and Fridovich [12].

The 6-minute walk test will be conducted on a 30-meter flat track, demarcated every three meters. Before starting the test, patients will remain seated for 10 min to stabilize vital signs. The patient will be advised to walk for 6 min, from one end of the lane to the other, at the highest possible speed. This test will be performed before the HD session, since patients cannot walk well after the HD session due to the loss of fluid with hypotensive effects [13].

The static strength testing of lower limbs will be performed with a Crown® brand dynamometer. Initially, patients will be instructed to stand on the base of the device, flexed knees forming an angle of approximately 120°, upright spine, arms along the body and extended elbows. After resetting the instrument, the subjects should perform the maximum knee extension force possible, avoiding any movement with the spine or arms and moving the body backwards. Two measurements will be performed with a 1 min interval between them. The mean of these two measures will be used as a result [14].

After baseline collection, participants will be allocated randomly: 1) BFRG; 2) EG; 3) CG. The intervention will last twelve weeks divided into three weekly sessions, always having at least a day interval between sessions. All physical exercise sessions will be monitored by physical therapists and physical education teachers to guarantee the perfect execution of the exercises and the correct use of the BFR accessory and heart monitor.

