### Study variables

The dependent variables of the study will be the health indicators (AAI, strength, functional capacity and quality of life), inflammatory variables (IL-6, IL-10 and CRP), oxidative stress (catalase, superoxide dismutase and glutathione peroxidase) and femoral quadriceps muscle thickness. The independent variable will be BFR, and the variables alcohol intake, diet, age, BMI and use of continuous medication, will be collected and considered in the analysis as possible confounders (Table 1).

**Table 1 tbl0005:** Dependent and independent study variables.

Variables	Definition	Scala	Operationalization
*Dependent*			
Interleukin 6	**Numeric**	**pg/ml**	---
Interleukin 10	**Numeric**	**pg/ml**	---
C-reactive protein	**Numeric**	**pg/ml**	---
Femoral quadriceps muscle thickness	**Numeric**	**mm**	---
Catalase activity	**Numeric**	**U/mg**	---
Superoxide dismutase activity	**Numeric**	**U/mg**	---
Glutathione peroxidase activity	**Numeric**	**U/mg**	---
Ankle-arm index	**Numeric**	**Ratio**	---
Functional test	**Numeric**	**Meters**	---
Strength	**Numeric**	**Lbs**	---
Quality of life	**Numeric**	**Score**	---
*Independent*			
Continuous moderate exercise intervention associated with partial blood flow restriction	Trichotomous	0, 1 or 2	**0 – Without exercise**

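### Kruskal-Wallis for the non-parametric variables has no time factor or baseline adjustment, and its input is not stated; baseline-adjusted ANCOVA on logs would suit the cytokines and CRP better

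*Protocol article*

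**What the plan says.** All references are to the Protocol article.

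- **Data processing and analysis** assigns a mixed two-factor ANOVA with Bonferroni post-hoc comparisons to parametric variables. For the rest: "Kruskal-Wallis test and Dunn's post-hoc test will be used to non-parametric variables". The level is fixed as "The 5% significance level will be used". The section does not say whether final values, changes or all visits enter Kruskal-Wallis, or which outcomes count as non-parametric.
- **Abstract** states the comparison: "Baseline measures will be compared with final measures".
- **Procedures** makes the blood markers repeated measures. Samples are taken at baseline, after the third training session (linked there to lactate), and "at the end of weeks six and twelve, respectively".
- **Study variables** lists among the dependent variables the "inflammatory variables (IL-6, IL-10 and CRP"). Table 1 gives every dependent variable as numeric and assigns none to either test.
- **Randomization** is blocked by HD shift.
- **Sample size calculation** says "36 patients would be required (to maintain a minimum power of 80% and a 95% confidence level") and "To compensate for possible losses and refusals, 42 patients will be included". With three groups that is 12 and 14 per arm if equal.

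**The concern.** The two branches of the analysis are not counterparts. The mixed ANOVA has group and time as factors, and its interaction asks whether change differs between groups. Kruskal-Wallis is the rank version of a one-way ANOVA: one factor, one independent value per patient, no covariate. An outcome sent to this branch loses the time factor. Unless change scores are the input, it also loses the baseline measurement. The question then moves from a difference in change to a difference in final level.

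Positive concentrations such as IL-6, IL-10 and CRP are plausible candidates for this branch, and they are central to the trial's aim. With about 14 patients per arm, the baseline value is the cheapest source of precision available, and it is already being collected. What is at stake is power for these markers, and whether a reader can tell what was tested.

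**Working it through.** **The plan's own figure.** The 36 patients cannot be reproduced, because the article gives no effect size, SD or test. Working backwards, a one-way ANOVA with three groups, 36 patients, 80% power and a 5% level implies Cohen's f = 0.54. If one of three equal arms is shifted by δ SD, f = δ√2/3, so δ = 0.54 × 3/√2 ≈ 1.15. A shift of about 1 SD is therefore of the order the sample size can detect.

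**Inputs from the article.** Three arms; 14 per arm (42/3) or 12 per arm (36/3); 5% level.

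**Assumptions, since the article gives none.** One arm shifted by 1.0 SD on the log scale; baseline-final correlation ρ of 0.3, 0.5 or 0.7; log-SD 0.8, which matters only for change on the raw scale.

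**Why baseline matters.** On the log scale, with unit SD, the variance v that the group comparison faces is:

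- final value alone: v = 1
- change: v = 2(1 − ρ) = 1.4, 1.0, 0.6
- ANCOVA: v = 1 − ρ² = 0.91, 0.75, 0.51

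The non-centrality is λ = n × (2/3) × δ²/v. With n = 14 and δ = 1 this is 9.33/v:

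- final: λ = 9.33
- change: λ = 6.67, 9.33, 15.56
- ANCOVA: λ = 10.26, 12.44, 18.30

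The non-central F distribution (2 and 39 degrees of freedom; 2 and 38 for ANCOVA) gives power of 75.2% for an ANOVA of final values, 59.7%, 75.2% and 93.5% for change, and 79.3%, 86.8% and 96.6% for ANCOVA. The ANCOVA figures are slightly optimistic because they ignore chance baseline imbalance.

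**Simulation of the tests themselves** (20,000 runs, 14 per arm, 1.0 SD; power in %):

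| Analysis | ρ = 0.3 | ρ = 0.5 | ρ = 0.7 |
|---|---|---|---|
| Kruskal-Wallis, final value | 72.2 | 71.5 | 72.4 |
| Kruskal-Wallis, raw change | 60.8 | 74.3 | 91.5 |
| Mixed-ANOVA interaction, logs | 59.8 | 74.8 | 93.4 |
| ANCOVA, logs | 78.0 | 85.7 | 96.1 |
| ANCOVA, ranks | 75.7 | 82.9 | 93.5 |

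The simulation agrees with the formulas.

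- ANCOVA on logs minus Kruskal-Wallis on final values: 5.8, 14.2 and 23.7 points.
- ANCOVA on logs minus Kruskal-Wallis on change: 17.2, 11.4 and 4.6 points.
- Rank ANCOVA minus Kruskal-Wallis on final values: 3.5, 11.4 and 21.1 points. This isolates the value of baseline while staying on ranks.

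With 12 per arm and a 1.15 SD shift, Kruskal-Wallis on final values has 77%, against 83%, 89% and 98% for ANCOVA on logs. On change it has 67%, 80% and 94%, against 65%, 80% and 96% for the mixed-ANOVA interaction.

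**False-positive rate.** With no true effect, Kruskal-Wallis gives 4.7 to 4.9% on final values and 4.4 to 5.0% on change. ANCOVA on logs or ranks gives about 5%.

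**The case against.** The strongest defence is that Kruskal-Wallis on each patient's change is an obvious reading. It uses one value per patient, keeps baseline, is valid, and performs about as well as the plan's own ANOVA interaction. The article neither states nor excludes it, and a condensed article may leave the input of a named test to a fuller document. This stands: Kruskal-Wallis is not incapable of addressing a baseline-versus-final question.

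It also stands that the power loss is measured against ANCOVA, which the article uses for no outcome. Against the plan's own interaction test, Kruskal-Wallis on final values is better at ρ = 0.3 (72% against 60%), slightly lower at 0.5 (72% against 75%) and clearly worse only at 0.7 (72% against 93%).

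Three stronger readings are tempting and lack support:

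- **Inflated false positives.** If visits were stacked as independent observations, the error rate would be 10 to 19% with two visits (ρ from 0.3 to 0.8). Nothing in the article says visits will be pooled.
- **A normality-driven switch.** The article names no normality test or switching rule. A reader may suspect one, because no outcome is assigned in advance, but it is not stated.
- **Lost covariates as a Kruskal-Wallis defect.** Study variables says confounders will be considered, and Kruskal-Wallis cannot take them. But the ANOVA as described lists no covariates either, so this does not separate the two methods.

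What the defence leaves untouched is that the named test has one factor, that its input is open, and that neither valid input uses baseline as well as an adjusted analysis does.

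**Conclusion.** The point holds as one of efficiency and clarity. As written, the test for non-parametric variables does not match the group-by-time analysis of the other variables or the stated comparison, and the reader cannot tell what will be tested. Under the assumed 1 SD shift with 14 per arm, the cost against baseline-adjusted ANCOVA on logs is about 6 to 24 points of power if final values are used and about 5 to 17 points if changes are used. The loss grows with the correlation in the first case and shrinks with it in the second. These sizes rest on assumed effect size, log-SD and correlation; that these markers are skewed enough to take this branch is also an assumption. The documents do not support a claim that the planned test is invalid.

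**What to change.** For IL-6, IL-10 and CRP, replace Kruskal-Wallis and Dunn with a pre-specified ANCOVA of the log final value on group, log baseline and HD shift. Report ratios of geometric means with confidence intervals, and Bonferroni-adjusted pairwise contrasts. State which blood sample is the final value. Pre-specify rank ANCOVA (ranks of the final value adjusted for ranks of baseline and for shift) as a sensitivity analysis to be reported regardless, not as a fallback chosen after looking at the residuals. If any other outcome is to stay with Kruskal-Wallis, name the outcome and the value that enters the test.

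The cost is a change of wording in the analysis section. Baseline samples and shift are already recorded, and no patients or visits are added. The downside is that results for these markers are ratios rather than raw differences, and that they come from a different model from the mixed ANOVA kept for the other outcomes.
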